## Abstract

**Background:**

Early-onset preeclampsia (eoPE), defined as preeclampsia occurring before 34 weeks of gestation, remains one of the leading causes of severe maternal morbidity, iatrogenic prematurity, and maternal mortality worldwide. Its heterogeneous and rapidly evolving clinical course makes the prediction of adverse outcomes particularly challenging. Although machine learning (ML)–based models have shown promise in stratifying eoPE risk and supporting clinical decision-making, robust prospective external validation is still lacking. The present study aims to address this gap through a multicenter validation of three ML models previously developed by our group to: (1) predict maternal complications, (2) estimate the likelihood of delivery within ≤ 7 days of diagnosis, and (3) identify the risk of hemolysis, elevated liver enzymes, and low platelets (HELLP) syndrome or placental abruption.

**Methods:**

This prospective multicenter cohort study (2024–2027) recruits pregnant women diagnosed with eoPE after informed consent. Clinical, analytical, and ultrasound data, including all variables used in the models, are recorded from early pregnancy to delivery. The first 100 cases will undergo quantitative external validation of three ML models and a semi-quantitative evaluation by clinicians, after which these cases will be used to retrain the models. The updated models will then be prospectively applied to the next 100 participants. Model predictions and physician´s assessment of the clinical utility of such predictions are generated through a secure web application accessible only after delivery.

**Discussion:**

This study addresses a critical gap in the prospective validation of ML-based tools for eoPE, emphasizing methodological rigor, data quality, and external validation in a multicenter setting. By integrating quantitative performance assessment with clinician-centered evaluation, the project seeks to ensure both statistical robustness and real-world clinical relevance. If successfully validated, these models could support more individualized and timely decision-making in eoPE management.

**Supplementary Information:**

The online version contains supplementary material available at 10.1186/s12884-026-09424-3.

## Background

Preeclampsia (PE) is a hypertensive disorder of pregnancy characterized by the de novo onset of hypertension after 20 weeks of gestation, accompanied by proteinuria or evidence of end-organ dysfunction or fetal growth restriction (FGR) [1]. Complications such as eclampsia, placental abruption and hemolysis, elevated liver enzymes, and low platelets (HELLP) syndrome leading to life-threatening conditions like liver hematoma and disseminated intravascular coagulation, make PE one of the leading causes of maternal morbidity and mortality worldwide. The incidence of PE is estimated at 2–5%, and it accounts for approximately 50,000 maternal deaths each year, 99% of which occur in low- and middle-income countries [2, 3]. Optimizing antenatal care to prevent disease progression is therefore essential to mitigate the severity and adverse outcomes associated with the disorder [4]. However, delivery remains the only definitive treatment, making early forms of PE the leading cause of iatrogenic prematurity [5, 6]. Early-onset preeclampsia (eoPE), defined as PE occurring before 34 + 0 weeks of gestation, accounts for about 20% of all cases and is associated with a tenfold increase in maternal mortality and a fourfold increase in severe maternal morbidity [7].

In eoPE, an excess of antiangiogenic factors—particularly soluble fms-like tyrosine kinase-1 (sFlt-1)—is released into the maternal circulation, reducing the bioavailability of proangiogenic factors such as placental growth factor (PlGF). The resulting angiogenic imbalance induces systemic endothelial dysfunction, which underlies the multiorgan involvement characteristic of the disease [8]. An elevated sFlt-1/PlGF ratio has been consistently associated with the onset and severity of eoPE [9] and shows an inverse correlation with the time to delivery [10]. These findings highlight the potential role of angiogenic biomarkers for improving clinical risk stratification.

The clinical management of eoPE remains complex, as clinicians must balance the maternal risks of disease progression against the potential neonatal benefits of pregnancy prolongation. In the absence of complications, most international guidelines recommend delivery at 34 weeks’ gestation to optimize neonatal outcomes [11]. However, prolonging pregnancy to reach this threshold carries significant maternal risks [12]. Observational data indicate that approximately one in three women managed expectantly experiences a major maternal complication requiring intensive care, including HELLP syndrome (12%), placental abruption (11%), pulmonary edema (3%), or renal failure (4%) [13]. The strategy of continuing pregnancy until 34 weeks is based primarily on two clinical trials conducted in the 1990s [14, 15], and a subsequent systematic review incorporating more recent studies concluded that further evidence is needed to establish its safety for the mother [12]. Even under optimal conditions and with careful case selection, the median duration of pregnancy prolongation achieved through expectant management is around seven days (standard deviation: 2–18 days) [14]. While this short gain may be crucial for neonatal outcomes in extremely preterm stages, its benefit becomes less justifiable beyond 30 weeks, when neonatal survival rates in tertiary centers reach 97% at 30–32 weeks (90% without severe morbidity) and 99% at 32–34 weeks (98% without severe morbidity) [16–18].

Another clinical difficulty lies in the administration of corticosteroids for fetal lung maturation. A complete course administered within the week prior to birth significantly reduces neonatal morbidity and mortality, with an adjusted odds ratio of 1.46 (95% CI: 1.20–1.77) compared to administration more than a week before delivery [19]. However, repeated courses appear to be counterproductive, particularly in the long term [20]. Current recommendations therefore favor a single course administered within seven days of delivery [21], a goal that is difficult to achieve in eoPE because of the unpredictable rate of disease progression [22].

Together, these clinical uncertainties underscore the need for accurate, individualized tools capable of predicting the short-term risk of maternal complications and the likelihood of requiring delivery in the days following diagnosis. Several predictive models have been developed to assist clinicians in estimating the risk of complications in PE, although their applicability to eoPE remains limited [23, 24]. The most popular is the PIERS model. Although initially promising, it has shown some limitations. Validation studies have demonstrated that its performance is highly dependent on the case-mix and healthcare setting [25–28]. Additionally, its predictive horizon is restricted to 48 h, as it relies on variables that are direct indicators of established organ dysfunction (rather than angiogenic markers), thus offering limited usefulness for anticipating disease progression [29].

On the other hand, Machine Learning (ML) offers a promising approach to address this challenge, as it can capture complex, nonlinear interactions among clinical, ultrasound, and laboratory variables (including angiogenic markers) while minimizing human bias in interpretation [23]. Building on our previous work [13], our group recently developed a ML–based ensemble model using a cohort of 234 patients diagnosed with eoPE. Within this framework, women diagnosed with eoPE are initially assessed using the main model, “Risk of Adverse Outcomes” (R), which estimates the probability of developing any of six major maternal complications: pulmonary edema, renal failure, refractory hypertension, neurological events, HELLP syndrome, or placental abruption. For those classified as high risk, two additional predictive models are subsequently applied: the “Time to Delivery” (T) model that predicts the need for delivery within seven days of diagnosis and the “HELLP-Abruption” (HA) model that estimates the risk of these two acute and unexpected adverse outcomes. This ensemble modeling framework is designed to support individualized decision-making regarding timely hospitalization, corticoid administration and delivery [30].

The development process required addressing the complexity and heterogeneity of the dataset so a structured feature–selection pipeline was implemented using genetic algorithms (GAs), an evolutionary computation technique capable of efficiently searching high-dimensional feature spaces. Two complementary strategies were applied: a mono-objective GA aimed at maximizing the F1-score of each classifier, and a multi-objective GA (NSGA-II) that simultaneously optimized predictive performance and model parsimony, favouring solutions with fewer variables to enhance clinical feasibility [31]. The three models underwent internal validation and demonstrated promising diagnostic performance (sensitivity and specificity of 70%/74%, 69%/88% and 88%/69%, respectively). The R model (K-Nearest Neighbor) included twenty-five predictive variables, the T one (Logistic Regression) included fourteen, whereas the HA (Logistic Regression) incorporated thirteen. Subsequently, simplified versions of the models were derived from the multi-objective strategy: based on only five, seven and three features, achieving a sensitivity of 60%/68%/92% and a specificity of 74%/86%/52% (Fig. 1) [30]. Although the HA model prioritizes sensitivity over specificity, this trade-off may be clinically acceptable, particularly between 30 + 0 and 33 + 6 weeks of gestation, when the maternal risks of continuing the pregnancy increase while neonatal outcomes improve rapidly with gestational age.

**Fig. 1 Fig1:**
[figure not shown]
Overview of the machine learning models to be validated. For each model, the classification approach, the input variables used, and the results obtained during the development phase are presented. MCAPIp5_echo: Pulsatility index in the middle cerebral artery < percentile 5; GA_PE: Gestational age at preeclampsia onset; NumDrug: Number of antihypertensive administrated drugs; PIrUtA_echo: Pulsatility index of the right uterine artery; previous_PE: Preeclampsia in previous gestations; PlGF5: Angiogenic marker < percentile 5 for gestational age according to Verlohren et al. [32]; RatioScale: Clinical classification of sFlt-1/PlGF relation (0–38: normal; >38–85: suspicion of preeclampsia; >85–655: consistent with a diagnosis of preeclampsia; >655: high-risk of preeclampsia-related complications); weight: Pre-gestational weight; EFWp_echo: Customized percentile of estimated fetal weight; PIlUtA_echo: Pulsatility index of the left uterine artery; chronic_ht: Maternal chronic hypertension; mPIUtAMoM: Multiples of the median of the mean pulsatility index of the uterine arteries; sFLt195: Antiangiogenic marker > percentile 95 for gestational age according to Verlohren et al. [32]; PlGFscale: Clinical classification of PlGF

Despite these encouraging findings, external validation in a broader and more heterogeneous population is essential before these models can be considered for clinical implementation. The present study aims to address this need assessing the diagnostic accuracy, calibration, and clinical utility of the models across multiple hospitals participating in the Spanish RICORS-SAMID network.

## Methods

### Study setting

This is a prospective, multicenter, observational cohort study that is conducted at six Spanish sites including Hospital Universitario 12 de Octubre in Madrid, Hospital Sant Joan de Déu and Hospital de la Santa Creu i Sant Pau in Barcelona, Hospital Universitario Cruces in Barakaldo in Bizkaia, Hospital Lozano Blesa in Zaragoza, Hospital Universitario Virgen de La Arrixaca in Murcia and Hospital Universitari i Politècnic La Fe in Valencia. Additionally, Hospital Universitario Puerta del Mar in Cádiz are planned to be incorporated soon.

### Dates of the study

The study is planned to run from 2024 to 2027 and is currently in the recruitment phase. Participant recruitment began on October 1, 2024, and is expected to be completed by the end of 2026. Data will be collected in parallel with patient recruitment, from the beginning of pregnancy until delivery. The data collection period will then be extended for an additional two months to complete follow-up for the last enrolled participants, ensuring that all required information is available for the final analysis. Results are expected by May 2026.

### Objectives

The primary objective of this study is to externally validate the diagnostic performance and clinical usefulness of three ML–based models designed to predict (1) maternal complications, (2) the need for delivery within ≤ 7 days of diagnosis, and (3) the development of HELLP syndrome or placental abruption.

Secondary objectives of this study include:

Improvement of the prediction models by incorporating data from 100 new eoPE cases into the ML training process.Adjustment of the training process to specifically train and optimize the models for the eoPE subgroup with the greatest potential for applicability due to their clinical interest in management: PE diagnosed between 30 + 0 and 33 + 6 weeks of gestation.Conduct a semi-quantitative post-hoc assessment of healthcare professionals’ satisfaction with the information provided by the models to adjust the timing of (1) fetal maturation with corticosteroids, (2) hospitalization, and (3) pregnancy termination.Development of a web application that integrates the data collection and validation process (both quantitative and semi-quantitative) into a single tool accessible to clinicians.

### Inclusion criteria

Eligible patients are pregnant women meeting all of the following criteria: (1) maternal age ≥ 18 years; (2) singleton pregnancy; (3) diagnosis of PE established according to the criteria of the International Society for the Study of Hypertension in Pregnancy [11]; (4) gestational age at the time of diagnosis between 20 + 0 and 33 + 6 weeks; (5) availability of angiogenic biomarker results (sFlt-1/PlGF ratio) obtained at the time of diagnosis (± 3 days); and (6) provision of written informed consent to participate in the study.

### Exclusion criteria

Patients will be excluded if: (1) do not provide written informed consent to participate in the study; (2) fetal congenital malformations are present, such as severe structural anomalies, genetic disorders, or confirmed congenital infections; (3) delivery occurs at a non-participating center.

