### Sample size estimation

We will evaluate 5 candidate predictors for the R model, 7 for the T model, and 3 for the HA model as specified in Fig. 1. Following the recommendation of having at least 10 events per predictive variable and assuming that:

Approximately 50% of women with eoPE deliver within ≤ 7 days [14], the required sample size to validate the T model is: 7 (predictive features) x 10 (events) / 0,5 (event incidence) = 140 eoPE casesApproximately 40% of women with eoPE experience any PE-related complication, and in 20% these complications include placental abruption or HELLP syndrome [30]. According to this, the required sample size to validate the R model is: 5 (predictive features) x 10 (events) / 0,4 (event incidence) = 125 eoPE cases, and to validate the HA model is: 3 (predictive features) x 10 (events) / 0,2 (event incidence) = 150 eoPE cases

This estimation assumes independence among predictor variables. However, ML techniques can identify dependencies between variables when present, which could potentially reduce the required sample size. Nonetheless, we have chosen to maintain the estimate of 200 cases, as it is the most conservative assumption and aligns with the sample size used in our previous work during model development, providing greater confidence.

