### Study variables

#### Dependent variables

Below are the outcomes assessed in each model:R Model: presence of at least one of the following adverse maternal events (yes/no):◦ Pulmonary edema confirmed radiologically and associated with oxygen saturation <95%.◦ Acute kidney injury (creatinine ≥1.6 mg/dL or an increase ≥1.0 mg/dL from baseline) or oliguria (<500 mL/24 h).◦ Refractory hypertension: severe and uncontrolled elevation of blood pressure for >12 hours despite the use of at least three antihypertensive medications.◦ Neurological events: hemorrhagic stroke, coma (Glasgow Coma Scale <13), posterior reversible encephalopathy syndrome, or cortical visual loss including retinal detachment.◦ HELLP syndrome: hemolysis (bilirubin ≥1.2 mg/dL, LDH ≥600 IU, or diagnosis by peripheral smear), elevated transaminases (AST ≥70 IU/L), and platelet count <100,000/mm³. Cases meeting two of the three criteria (incomplete HELLP) will also be included.◦ Placental abruption: partial or complete separation of the placenta from its normal uterine implantation site before completion of the second stage of labor. Diagnosis requires evidence of an organized retroplacental hematoma involving at least 20% of the implantation area.T model: interval between the diagnosis of eoPE and delivery ≤7 days (yes/no)HA model: presence of HELLP syndrome or abruptio placentae (yes/no)

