### Study regimen

The study will follow the steps outlined in Fig. 2. First, pregnant women who meet the eligibility criteria will be identified at each participating center. They will receive both verbal and written information explaining the purpose and procedures of the study and will be invited to participate. After consent, the investigator will register the case in the REDCap™ database [33], hosted by the Research Institute of Hospital 12 de Octubre (i + 12), by selecting the appropriate center in the “Data Access Group,” which automatically generates a unique study identifier. All relevant clinical, analytical, angiogenic, and ultrasound data, from early pregnancy through delivery, will be collected and entered into the corresponding REDCap™ sections. Only once delivery has occurred will the clinician access the web application to obtain the model predictions and complete the semi-quantitative assessment, following the procedure detailed in the “Web Application” section.

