### Data collection

Data collection constitutes a critical phase of the study, as the quality and completeness of the information recorded will directly determine the robustness and validity of the subsequent external validation analyses. Study data are entered and managed is performed through a dedicated database developed for this purpose on the REDCapTM platform. It allows participating centers to create and complete electronic case report forms in real time and supports data import and export in multiple formats, including Microsoft Excel, PDF, SAS, Stata, R, and SPSS.

The designated clinician at each participating center will be responsible for recording all patient data in REDCap™, covering the period from the start of pregnancy until delivery. Each participant will be assigned a unique identification code that decouples clinical data from personally identifiable information. The linking file containing the correspondence between study codes and personal identifiers will be stored securely and accessible only to a limited number of authorized persons. Thus, the data complies with the Personal Data Protection and Guarantee of Digital Rights and Regulation (EU) 2016/679 of the European Parliament and of the Council of April 27, 2016 on Data Protection (GDPR).

In this sense, the first and last sections of the database are particularly important and are described in detail in Additional file 1. In the first section (“Patient ID”), the clinician must enter the patient’s medical record number (MRN), which is immediately encrypted to ensure full anonymization. The clinician must also confirm that the inclusion and exclusion criteria are met and record the date on which informed consent was signed.

In the final section (“Semi-quantitative assessment”), a link to the web application is provided. The appearance of the application interface is shown in Additional file 2. Once the data used by the models and the delivery information have been entered into the database, the clinician can access the application to obtain the model outputs and complete the semi-quantitative assessment. Both the model outputs and the clinicians’ responses will be automatically stored in this section under the corresponding patient’s record. This retrospective appraisal minimizes optimism bias and allows the evaluation to reflect the clinical value of the predictions rather than responses influenced by the models themselves.

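### Place of delivery is listed as an exclusion criterion, although it is known only after enrolment, so consented women can be removed from the validation in a way that may depend on their outcome

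*Protocol article*

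**What the plan says.** The third exclusion criterion in the Protocol article (Exclusion criteria) applies when "delivery occurs at a non-participating center". It refers to where delivery actually takes place, not to where it is planned.

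The rest of the article places eligibility before delivery:

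- The abstract says that the study "recruits pregnant women diagnosed with eoPE after informed consent".
- Study regimen gives the order: "First, pregnant women who meet the eligibility criteria will be identified at each participating center". Information and consent follow, and then: "After consent, the investigator will register the case in the REDCap™ database".
- Data collection describes the first database section, which holds the patient identifier. There, "The clinician must also confirm that the inclusion and exclusion criteria are met and record the date on which informed consent was signed".
- Dates of the study has data gathered "from the beginning of pregnancy until delivery", with two further months to complete follow-up of the last women enrolled.

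All three model outcomes (Dependent variables) arise after diagnosis. T is whether delivery follows diagnosis within seven days. R is any of six maternal complications. HA is HELLP syndrome or abruption.

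**The concern.** The models are meant to be used at diagnosis, so the cohort that validates them should be fixed by what is known at diagnosis. Criterion 3 depends on a later event. For a woman who is still pregnant, a site cannot truthfully confirm it when it confirms the other criteria. In practice it is a rule for removing women who have already consented and been registered.

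That would be harmless if place of delivery were unrelated to the outcomes, but there are plausible reasons why it may be related. For T, a woman who delivers soon after diagnosis at a participating hospital has little time to deliver elsewhere, and one with a longer interval has more. Sudden deterioration that leads to delivery at another hospital would act in the opposite direction.

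If losses differ by outcome, the event rates and predictive values in the retained cohort are biased. Calibration may be too. Sensitivity and specificity are also biased if, within an outcome group, losses are related to the predicted risk. The first 100 cases are also used to retrain the models (Models' validation strategy), so any selection would carry into the updated models and into their comparison with the original ones.

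**Working it through.** **1. Sample size, to set it aside.** The article's rule is predictors × 10 / event incidence.

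- T: 7 × 10 / 0.5 = 140
- R: 5 × 10 / 0.4 = 125
- HA: 3 × 10 / 0.2 = 150

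All three match Sample size estimation. With 200 enrolled, the largest requirement on that rule is met until losses exceed 1 − 150/200 = 25%. The issue is selection, not numbers.

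**2. Inputs for the illustration.**

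- T event rate 0.50, from Sample size estimation: "Approximately 50% of women with eoPE deliver within ≤ 7 days".
- Simplified T model, sensitivity 68% and specificity 86%, from Background.
- Share x removed under criterion 3: not given, assumed 5% or 10%.
- Share of removed women without the T event: not given, assumed 80%.
- T scored in every woman: assumed. Under Workflow, the web application runs T and HA only when the R prediction exceeds 0.5.

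**3. Formulas.**

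- Retained event rate p = (0.50 − 0.2x) / (1 − x)
- NPV = 0.86(1 − p) / [0.86(1 − p) + 0.32p]

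**4. Results.**

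| x | p | NPV |
|---|---|---|
| 0 | 50.0% | 0.430/0.590 = 72.9% |
| 5% | 0.49/0.95 = 51.6% | 71.6% |
| 10% | 0.48/0.90 = 53.3% | 70.2% |

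**5. Other directions.**

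- Equal removal, 5% in each outcome group: event rate, PPV and NPV stay at 50.0%, 82.9% and 72.9%.
- Opposite direction, 10% of women delivering within seven days and 2% of the others: event rate 0.45/(0.45 + 0.49) = 47.9%, PPV 81.7%, NPV 74.5%.

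**6. Sensitivity.** Take 100 T events, 68 of them detected.

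- If 2, 4 or 6 undetected events are lost, apparent sensitivity becomes 68/98 = 69.4%, 68/96 = 70.8% or 68/94 = 72.3%.
- If the same numbers of detected events are lost, it becomes 66/98 = 67.3%, 64/96 = 66.7% or 62/94 = 66.0%.
- If losses follow the 68/32 split, it does not move.

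The effect on calibration has not been calculated.

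**The case against.** **The link with disease course is inferred.** A reader might conclude that women leave the validation because of how their disease progressed, or that the criterion inflates sensitivity. The article supports neither as fact. It does not say why or how often women deliver elsewhere, the two mechanisms pull in opposite directions, and some moves may have nothing to do with the disease. Predictions are shown only after delivery, so they cannot themselves influence where a woman delivers. This stands, and it limits the point to a risk of bias of unknown sign. Place of delivery is a post-baseline event that may be related to the outcomes; it is not itself one of them.

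**Outcomes may be hard to verify.** A reader might infer that R and HA can simply be read from an outside discharge summary. Dependent variables does not support that. Abruption needs a hematoma of at least 20% of the implantation area, refractory hypertension more than 12 hours on at least three drugs, and HELLP and kidney injury specific laboratory limits. This stands as a reason for missing R or HA outcomes. It is no reason for ineligibility, and it does not touch T, which needs only the delivery date.

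**The clinician survey.** A clinician who did not manage the delivery may be unable to answer the question on its timing. This also stands, but only for the survey.

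**Size.** The illustrated shifts are modest. The 95% margin on a sensitivity of 68% with 100 events is 1.96 × √(0.68 × 0.32/100), or about ±9 points. That bears on how serious the point is, but it does not remove a systematic error.

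**A loosely labelled removal rule.** The article does not say that the first database section is locked at consent, and how removals are counted may be set out in the full protocol. That is fair, and the absence of such detail is not held against the plan. The difficulty is that a stated eligibility criterion rests on a later event.

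**Conclusion.** The point holds as a design weakness that should be corrected. What the text establishes is that criterion 3 depends on an event after enrolment, cannot be confirmed for a woman who is still pregnant, and so removes consented women after the prediction time. That removal is related to outcome is plausible, most directly for T, but it is not documented.

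Under the assumptions shown, the T event rate moves by 1.6 to 3.3 points and NPV by 1.3 to 2.7 points. The opposite pattern reverses the sign, and removal unrelated to outcome has no effect on either. These figures are illustrative: they rest on assumed rates of loss and on T being scored in all women. The sensitivity figures additionally require losses to fall unevenly on detected and undetected cases. No estimate of the actual bias can be drawn from the article.

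**What to change.** 1. Remove criterion 3 from the exclusion criteria, and define the cohort as all consenting women who meet the remaining criteria at diagnosis.
2. Score the models for every such woman from the diagnostic data already in the study database.
3. For women who deliver elsewhere, obtain the delivery date, which settles T, and request the delivering hospital's records for R and HA.
4. Where the stated outcome definitions cannot be verified, classify R or HA as a missing outcome. Report how many women this concerns and their baseline features, and run a sensitivity analysis.
5. Allow the clinician survey to be recorded as not applicable for these women.
6. Recruitment is still under way, so apply the same approach to women already removed, if their consent covers it.

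The cost is a short amendment and one record request per woman who delivers elsewhere. The drawback is that R and HA will be less complete in these women. The sample size calculation does not change.
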